#### Blinding

Teachers will not be blinded to group assignment, as they will attend rope skipping workshops and need to implement the intervention. Participants will be notified about the existence of randomization and group allocation procedures, but they will be blinded to the study hypotheses. All research assistants and raters for the SOFIT protocol will also be blinded to the specific hypothesis of the study. They will not be specifically told about the randomization and allocation of groups, but we will not consider them to be completely blinded to these as they may rate classes from both experimental and control groups and hence may be able to ascertain that some classes are assigned specific tasks.

### Statistical methods

Multilevel modeling will be used to account for the effects of participant clustering. Specifically, a three-level (time within student within class) model will be examined. For our primary outcome of students’ percentage time spent in MVPA, the effects of group allocation and student gender on percentages of time spent in MVPA will be examined using a multilevel regression model. The group × gender interaction effect will also be examined to determine whether the effect of the intervention is homogeneous across genders. Further, we will also examine a model by adding perceived autonomy support, autonomous and controlled motivation as potential confounders of the outcome. Two-tailed tests with an alpha level of .05 will be used to determine the significance of all results. To examine whether the intervention would lead to changes in motivation variables and perceived autonomy support by teachers, these variables will be regressed on group, gender, and group × gender in an additional series of three-level regression analyses. Statistical analyses of the study will be conducted by a statistician blinded to the hypotheses of the study and to each class’ allocation to the experimental or control condition.

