**Methods/Design:**

A matched-pair cluster randomized controlled trial was designed. Secondary school students from 24 classes (from 12 schools) will be recruited to participate in the trial. Students’ baseline MVPA will be measured during school PE. Classes will be matched according to baseline variables and one class from each pair will be randomized into the experimental group. Teachers in the experimental group will be invited to attend a teacher workshop, and will insert a 15-minute rope skipping activity in four consecutive PE lessons. Motivational factors based on self-determination theory will also be measured as secondary outcomes. The effectiveness of the intervention will be evaluated by comparing changes in the proportion of lesson time spent in MVPA from baseline to follow-up across the experimental and control groups.

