### Outcomes

#### Primary outcome

The primary outcome of the study is the proportion of PE lesson students spend in MVPA. This will be measured using ActiGraph (Pensacola, Florida) GT3X + accelerometers. MVPA will be defined using Evenson and colleagues’ criteria [25], and 1-second epochs will be used [26]. Evenson et al.’s cutoff values were chosen because they were found to be more accurate than other commonly used cut points [27]. To test the validity and sensitivity of the devices of capturing non-lateral movements such as rope skipping, we invited 12 boys and girls with varying rope skipping experience perform rope skipping tricks (in 1-minute bouts with at least one minute rest in between) that will be included in the intervention while wearing accelerometers. For all skippers and for all tricks tested, the activity was classified as MVPA based on Evenson et al.’s cut points. In our formal trial, accelerometry measurements will be taken during the first three lessons at baseline (Lessons 1 to 3; see Figure 2). MVPA will be measured for the same sets of seven students in each class throughout the study. These students will be randomly selected by the investigators from class lists (not containing names of students) provided by teachers using a random number generator. The mean of each student’s proportion of time spent in MVPA during these three classes will be used as his or her baseline. The primary outcome will pertain to the individual level and will not be aggregated within the cluster.

After baseline assessments, classes will be randomized into either the experimental or the control group. Teachers of classes in the experimental group will be invited to attend the teacher workshop after Lesson 4, and before Lesson 5. Following the workshop, these teachers will implement the intervention in their class for four consecutive PE lessons (Lessons 5 to 8). For schools in the control group, teachers will conduct classes using their usual methods, which are not expected to include rope skipping. Post-test accelerometry measures will be taken during Lessons 5 to 7. The mean of each student’s MVPA percentages taken from these three classes will be used as follow-up scores. Similarly, this measure pertains to the individual level.

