### Sample size

Sample sizes were calculated based on the effect sizes calculated from Lonsdale et al.’s [6] systematic review and meta-analysis. In their study, Lonsdale et al. found that the standardized difference, or Cohen’s *d*, of fitness infusion interventions implemented within PE classes to be 1.4. Adopting a conservative approach, we based our power calculation on a projected effect of *d* = 1.0. The required sample size was calculated using GPower 3.1, with alpha level set to .05, and power at .80. The required sample size for a two-tailed independent sample t-test was found to be 34 students.

To account for the clustering nature of the data, the required sample size of 34 was adjusted by design effect [30] of 1 + (*m*-1)ρ, where *m* is the sample size of each cluster and ρ is the intraclass coefficient (ICC). In order to limit the disruptions to classes when distributing accelerometers, we decided to administer the device to seven students in each class. Aelterman et al. [15] found in their study that the ICC of MVPA between classes was .63. Using these estimates, the required correction factor is 1 + (7–1).63 = 4.78, meaning that the total required sample size is 163 (4.78 × 34 students). Therefore, 24 classes will need to be recruited for the study (24 classes × 7 students = 168 students).

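### The plan does not say which model term tests change in MVPA or whether class may vary over time: one reading can inflate the false-positive rate, the other roughly halves the effect

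*Protocol article*

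**What the plan says.** Under Statistical methods, the protocol article gives the aim, "Multilevel modeling will be used to account for the effects of participant clustering", and then the structure: "Specifically, a three-level (time within student within class) model will be examined". For the primary outcome, "the effects of group allocation and student gender on percentages of time spent in MVPA will be examined using a multilevel regression model", and a group × gender interaction is added. No time or group × time term is written, and no random effects are listed beyond the nesting. The same section fixes the error rate: "Two-tailed tests with an alpha level of .05 will be used to determine the significance of all results".

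The Abstract (Methods/Design) defines the evaluation as "comparing changes in the proportion of lesson time spent in MVPA from baseline to follow-up across the experimental and control groups". Under Primary outcome, "MVPA will be measured for the same sets of seven students in each class throughout the study", and each student gets one baseline score (the mean over Lessons 1 to 3) and one follow-up score (the mean over Lessons 5 to 7). Trial design makes the class the unit of randomisation, allocated 1:1. Sample size relies on a published study whose authors "found in their study that the ICC of MVPA between classes was .63", and plans "with alpha level set to .05, and power at .80".

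**The concern.** The abstract's comparison is a difference in change, and each student has two scores. In a model with a constant class effect, a constant student effect and an independent occasion residual, subtracting baseline from follow-up removes class and student together. What remains to test the arms against is the spread of individual changes. That is sound only if students in the same class do not change together.

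Here they probably do. The measured students in a class share their teacher and lessons. The Intervention section says a teaching unit typically lasts four lessons, so a whole class may move to a different activity between the two measurement periods. The clustering correction behind the sample size would then be missing from the test of the primary question. The alternative, reading the listed effects literally, protects the error rate but answers a different question from the one in the abstract.

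**Working it through.** **1. The plan's own sample size.** Inputs from Sample size: d = 1.0, two-sided alpha .05, power .80, m = 7, ICC = .63. A two-sample t-test has power .781 with 16 per arm and .807 with 17, so 34 students. Design effect = 1 + (7 − 1) × .63 = 4.78. Then 34 × 4.78 = 162.5, i.e. 163; 163 / 7 = 23.3, rounded up to 24 classes, or 168 students. The figures reproduce.

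**2. Reading A: group × time with random intercepts only.** For student i in class j at time t (0 or 1), with arm G:

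y = μ + βG + γt + δGt + u(class) + v(student) + e

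The change is D = γ + δG + (e₁ − e₀). Both u and v have gone. The model takes the variance of the estimated δ as σ²_D × (2/84), because each arm has 12 × 7 = 84 students. If changes within a class have intraclass correlation ρ_D, the true variance is larger by DE = 1 + 6ρ_D. The actual two-sided error is therefore

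α = 2[1 − Φ(1.96/√DE)]

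ρ_D is not in the article, so it is shown over a range. The simulated column is 20,000 null trials per row, 12 against 12 classes of 7, without matching.

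| ρ_D (assumed) | DE | SE too small by a factor of √DE | α, formula | α, simulated |
|---|---|---|---|---|
| 0 | 1.00 | 1.00 | 5.0% | 4.9% |
| .05 | 1.30 | 1.14 | 8.6% | 8.9% |
| .10 | 1.60 | 1.26 | 12.1% | 12.1% |
| .20 | 2.20 | 1.48 | 18.6% | 18.8% |
| .40 | 3.40 | 1.84 | 28.8% | 29.2% |
| .63 | 4.78 | 2.19 | 37.0% | 38.0% |

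**3. From the ICC of level to the ICC of change.** The .63 describes level. Let c be the correlation of class effects between periods and a that of student effects within class. Both are assumptions. Then

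ρ_D = .63(1 − c) / [.63(1 − c) + .37(1 − a)]

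With c = .8 and a = .5: .126 / (.126 + .185) = .405, which gives DE = 3.43 and α = 29%. With a = .5 throughout, c = 1, .95, .9 and .5 give α = 5%, 15%, 22% and 37%. Varying a from 0 to .7 gives 11% to 20% at c = .95 and 22% to 34% at c = .8.

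**4. Reading B: the group main effect.** With group, gender and group × gender only, group is a class-level covariate judged against between-class variance. A small check with fitted mixed models (113 null data sets, c = .8, a = .5) rejected 3.5% for the group main effect and 35% for group × time. Reading B is therefore not inflated. But no class is treated at baseline, so the expected group coefficient is (0 + δ)/2 = δ/2.

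**5. After correction.** Taking class mean changes as the unit, with t on 24 − 2 = 22 degrees of freedom, the simulated error is 4.9% to 5.2% at every ρ_D in the table. Using 1.96 in place of the t quantile gives 6.2% to 6.5%. For a follow-up comparison under the plan's own assumptions, 24 classes still have power .81 on 22 degrees of freedom.

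**The case against.** A reader might infer that the plan's model contains no class-by-time variance, that it therefore treats students as independent, and that the error rate is inflated several-fold. The article does not support that, for three reasons.

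First, the quoted sentence gives nesting only. A model with exactly those levels can carry a random time effect at class level, and the stated purpose is to account for clustering. A journal article may leave the list of random effects and the degrees-of-freedom method to the full plan. Second, no group × time term is written, and the effects that are written give a test without inflation. Third, the size depends on an ICC of change that is nowhere given. Inflation is nil if class effects are perfectly stable, and less than two-fold below an ICC of change of roughly .06. Matching on baseline MVPA also lowers the figures somewhat: simulated pairing on baseline class means (6,000 runs, a = .5) reduced the error from 37.7% to 32.2% at c = .5 and from 29.6% to 27.0% at c = .8.

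All of this stands, and it limits the point to a conditional one. It does not remove it. The article does more than leave detail out: it names the effects to be examined, and they do not include the contrast by which the abstract says the intervention will be judged. Retreating to the group main effect saves the error rate only by giving up that contrast.

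**Conclusion.** The point holds conditionally. As written, Statistical methods does not identify the test of change, and neither ready reading is satisfactory. Under group × time with random intercepts only, the nominal 5% becomes about 9% to 37% for an ICC of change of .05 to .63, a range assumed here and stated before allowing for matching. It stays at 5% only if that ICC is zero, which is unlikely when whole classes share lessons and teacher. Under the literal group main effect, the error rate is kept but the estimate is about half the intervention effect.

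Which reading the sponsor intends cannot be told from the article, so the claim is not that the trial's test is invalid. It is that the primary test must be fixed before analysis, because its validity or its meaning depends on a choice left open.

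**What to change.** State the primary test in one sentence, in one of two forms:

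- the follow-up score regressed on group, adjusted for the student's baseline score, with a class random intercept; or
- group × time in the three-level model, with a random time effect at class level.

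In either case use a small-sample method (Kenward-Roger or Satterthwaite) with degrees of freedom based on the 24 classes.

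Apply the same specification to the autonomous and controlled motivation models. The article gives no ICC for these, so no size is claimed. Perceived autonomy support, which Secondary outcomes aggregates to the class mean, should be analysed at class level with one value per class and period. If seven students each carried the class mean, their changes would be identical (ρ_D = 1, DE = 7), and the formula above gives 2[1 − Φ(1.96/√7)] = 46%.

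The change adds one model term or replaces the outcome record. It needs no further data and no more classes under the plan's own assumptions. The downside is a wider, correct confidence interval.

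### As listed, the three-level MVPA model has no group × time term; fitted literally, its group coefficient would estimate half the intervention effect, not the promised comparison of changes

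*Protocol article*

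**What the plan says.** - **Model (Statistical methods).** Three levels are named, with time lowest, then student, then class. For the primary outcome, "the effects of group allocation and student gender on percentages of time spent in MVPA will be examined using a multilevel regression model". Group × gender is added to see whether the effect is the same for boys and girls, and a further model adds motivation and autonomy support. No time or group × time term is listed.
- **Questionnaire outcomes (Statistical methods).** To look for changes in motivation and perceived autonomy support, "these variables will be regressed on group, gender, and group × gender in an additional series of three-level regression analyses". Again no term involves time.
- **Intended comparison (Abstract, Methods/Design).** Effectiveness is to be judged by "comparing changes in the proportion of lesson time spent in MVPA from baseline to follow-up across the experimental and control groups".
- **Scores (Primary outcome; Secondary outcomes).** Each student's MVPA is averaged over Lessons 1 to 3 for baseline and over Lessons 5 to 7 for follow-up. Questionnaires are completed after Lesson 4 and after Lesson 8.
- **Timing (Sequence generation).** Classes are matched, partly on baseline MVPA, and randomized after baseline.

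**The concern.** Group is fixed for a class throughout the study. In a model whose rows are a student's baseline and follow-up scores, a group term with no time interaction compares the arms averaged over both periods. In one of those periods nobody has received the intervention. Such a coefficient is neither the difference in change that the Abstract describes nor the difference during the intervention lessons on which the hypothesis under Objectives is framed.

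Group × gender has the same fault: pooled over both periods, it mixes moderation of the intervention effect with differences that existed before randomization. The motivation and autonomy-support models repeat the specification.

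If an analyst followed the text literally, the main estimate would be diluted and the test underpowered. If analysts departed from it, the article would not say which contrast is primary.

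**Working it through.** **1. The plan's own sample size.** Inputs are from Sample size: "based our power calculation on a projected effect of *d* = 1.0"; "with alpha level set to .05, and power at .80"; seven students per class; ICC .63. A two-sided two-sample t-test at d = 1.0 needs 17 per arm (power 0.807), so 34 in total, as stated. Design effect: 1 + 6 × .63 = 4.78. Then 34 × 4.78 = 162.5, rounded to 163; 162.5 / 7 = 23.2 classes, rounded to 24, giving 168 students. The figure reproduces.

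**2. What the time level can be.** MVPA is reduced to one baseline and one follow-up mean per student, and questionnaires are given at two points only. A time level therefore has two occasions: baseline and post-test.

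**3. Expected group coefficient.** Let the true arm difference be 0 at baseline (randomization comes afterwards) and δ at follow-up. With complete, balanced data:

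- Group, gender, group × gender (as listed; gender centred): (0 + δ)/2 = 0.50 for δ = 1.0.
- The same plus a time main effect only: still 0.50.
- Time and group × time added: interaction coefficient 1.00.

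In 2,000 simulated trials with correlation 0.5, the pooled contrast averaged 0.498 and the change contrast 0.996.

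**4. Power.** Effects are in SD units, with 12 classes of 7 per arm, treated as unmatched (22 df), and a two-sided .05 test ("Two-tailed tests with an alpha level of .05 will be used to determine the significance of all results"). Let c be the class-level and a the student-level baseline/follow-up correlation. The article gives neither, so both are assumptions.

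- Follow-up only: class-mean variance = .63 + .37/7 = .683; SE = √(2 × .683/12) = .337; 1.0/.337 = 2.96; power 0.81.
- Pooled group effect: variance = .63(1 + c)/2 + .37(1 + a)/14; SE = √(2 × variance/12); effect 0.5.
- Change contrast: variance = 2[.63(1 − c) + .37(1 − a)/7]; effect 1.0.
- Baseline-adjusted follow-up: variance = .683(1 − r²), with r = (.63c + .37a/7)/.683; effect 1.0.

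With a = 0.3:

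| c | Pooled SE | 0.5/SE | Power, pooled group effect | Power, change contrast | Power, baseline-adjusted follow-up |
|---|---|---|---|---|---|
| 0 | .241 | 2.07 | 0.51 | 0.53 | 0.81 |
| 0.3 | .272 | 1.84 | 0.42 | 0.67 | 0.84 |
| 0.5 | .291 | 1.72 | 0.38 | 0.80 | 0.90 |
| 0.7 | .308 | 1.62 | 0.34 | 0.94 | 0.97 |
| 1.0 | .333 | 1.50 | 0.30 | >0.99 | >0.99 |

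Varying a from 0 to 1 moves the pooled column by no more than about 0.03 (at c = 0, from 0.52 to 0.49). The simulation at correlation 0.5 gave power 0.36 for the pooled contrast, 0.80 for change and 0.81 for follow-up only.

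**The case against.** The article prints no equation. It does not say that the two occasions are pooled, or that time or baseline is left out. If group were coded as time-varying (0 for everyone at baseline) with a time effect, its coefficient would be 1.00, and adjusting for baseline would also avoid the halving. The Abstract and the stated purpose of the motivation models both speak of change, so a statistician reading the whole article might well fit group × time. Exact terms and coding are also commonly left to a full protocol or SAP, which is not shown.

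Much of this stands. A reader might infer that the investigators have chosen to test a pooled effect, or that the trial's result will be half its true size. The documents support neither: the halving is a consequence of the listed terms, and the Abstract suggests a comparison of change was meant. But this is more than omitted detail. The article names the levels and the effects, and those effects do not deliver its own comparison.

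Taking time to mean only the lessons within Lessons 5 to 7 does not rescue the text. Those lessons are averaged to one score, and the questionnaire models are also three-level with only two measurement points.

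A reader might also infer that chance baseline imbalance passes freely into the estimate. For MVPA, matching on baseline limits this. Motivation and autonomy support are not matching factors, so there the point remains.

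**Conclusion.** The stated model and the stated comparison conflict. Taken literally, the group coefficient would estimate half the intervention effect. That factor rests on one baseline and one follow-up record per student, no expected baseline difference and complete data; missing records would shift it somewhat. It does not depend on any correlation.

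The power figures do. About 0.30 to 0.51, against 0.81 for follow-up only, holds under the plan's d and ICC, assumed correlations, and classes treated as unmatched although the design pairs them. They show how much rests on naming the contrast and are not a forecast for this trial. Nor does it follow that the planned 80% power is lost: a baseline-adjusted follow-up analysis keeps or exceeds it across the assumed range.

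**What to change.** Name one primary contrast under Statistical methods. Either of these is valid:

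- **Long format:** add time and group × time, constrain the arms to be equal at baseline, and declare group × time the primary coefficient. Let class effects differ between occasions, so that class-level change is not counted as student-level noise.
- **Baseline-adjusted follow-up:** regress each student's Lessons 5 to 7 mean MVPA% on group, adjusting for baseline MVPA%, with gender and a class random intercept.

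The unconstrained change contrast also answers the Abstract's question, but it loses power when the correlation is low (0.67 at c = 0.3 in the table).

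Test gender moderation with group × time × gender in the first form, or group × gender in the second. Use the same form for motivation, and for autonomy support at the class level at which the article aggregates it.

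The cost is a few sentences of rewording. It needs no new data and no change to sample size or conduct.

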### Randomization

#### Sequence generation

Randomization and allocation to experimental and control groups will be conducted after baseline measures are taken. Matched-pairs cluster randomization will be used. That is, randomization and group allocation will be conducted at the cluster (i.e., class) level, Specifically, participating classes will be matched in comparable pairs in terms of 1) class gender, 2) students’ percentage of time spent in MVPA measured at baseline, and 3) whether rope skipping is included in the school’s original PE curriculum. Baseline measures will be dummy coded and sent to a statistician outside the research group, who will then randomize and allocate classes in experimental and control groups. This person will have no information regarding the participating schools or classes. The statistician will match the pairs and randomize classes into experimental and control groups using a random number generator. After randomization, teachers will be told the group allocation of their classes. The allocation mechanism, however, will be concealed to them.

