## Discussion

Researchers have shown that most students engage in insufficient MVPA during PE classes [8]. To address this issue in space-confined school environments, such as those in Hong Kong, we designed an intervention based on rope skipping to increase students’ MVPA during PE lessons. The protocol described above provided details of how the intervention will be implemented and evaluated. The evaluation of this protocol is important because although students are expected to spend a high percentage of time in MVPA during the 15-minute rope skipping activity, it remains to be seen if the intervention increases the overall proportion of lesson time spent in MVPA compared to existing lessons. For instance, the contents of existing PE lessons may provide students with similar exposures to MVPA. If student MVPA levels increased during the 15-minute period, compensation effects may exist such that students may be less active during portion of the lessons [31]. Further, the current protocol allows us to explore whether the intervention effect is homogeneous across boys and girls. This is important because boys and girls may have different preferences towards the type of activity or game played [32]; therefore, examining the interaction effect on boys and girls separately may assist in future interventions or school policies aimed at increasing students’ activity levels.

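### A .05 test of group × gender cannot determine whether the MVPA effect is the same in boys and girls; make it an exploratory estimate with class-based confidence intervals

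*Protocol article*

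**What the plan says.** The Statistical methods section gives the interaction both a purpose and a criterion. The purpose is: "The group × gender interaction effect will also be examined to determine whether the effect of the intervention is homogeneous across genders". The criterion, which covers every analysis, is: "Two-tailed tests with an alpha level of .05 will be used to determine the significance of all results".

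The Discussion is milder: "the current protocol allows us to explore whether the intervention effect is homogeneous across boys and girls". It adds that looking at the interaction may help later interventions or school policy.

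Two passages show at what level gender varies. Under Sequence generation, "participating classes will be matched in comparable pairs in terms of 1) class gender". Under Participants, schools must be co-educational and have a unisex policy for PE lessons.

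The Sample size section covers the overall effect only: "we based our power calculation on a projected effect of" d = 1.0, "with alpha level set to .05, and power at .80". It then inflates for clustering with an ICC of .63 and 7 measured students per class, and arrives at 24 classes.

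**The concern.** Homogeneity is a claim that no important difference exists. A two-sided significance test can give evidence of a difference, but failing to reach .05 is not evidence that there is none. The purpose and the criterion in the Statistical methods section therefore do not fit each other.

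The mismatch matters more because of the design. If each class has one gender, gender is constant within a class and within a matched pair. The interaction then rests on 24 classes divided among four cells, not on 168 students, and the trial was sized for a different contrast. A non-significant interaction would be the likely result even if boys and girls responded quite differently.

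The protocol itself gives reasons to expect a difference. The Background notes that girls in particular enjoyed rope skipping, and the Discussion notes that the sexes may prefer different activities.

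**Working it through.** **Inputs from the protocol.** Sample size: d = 1.0, two-sided alpha .05, power .80, ICC .63, 7 students per class, 24 classes. Trial design: 1:1 allocation by class, so 12 classes per arm.

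**Assumptions.** Single-sex classes, 12 of boys and 12 of girls, so 6 per group-by-gender cell. The analysis is taken as one of class means, with 24 − 4 = 20 degrees of freedom. The total SD between students is set to 1.

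**The protocol's own figure.** A noncentral-t calculation for d = 1.0 gives 17 per arm, or 34 students, as stated. The design effect is 1 + (7 − 1) × .63 = 4.78. Then 34 × 4.78 = 162.5, rounded up to 163, and 163/7 = 23.3, which becomes 24 classes. The sample size reproduces.

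**Main effect with 24 classes.**
- Variance of a class mean = .63 + .37/7 = .683.
- SE = √(2 × .683/12) = 0.337 SD.
- Power for d = 1.0 with 22 df = 81%.

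**Interaction, no gain from baseline.**
- SE = √(4 × .683/6) = 0.675 SD, twice that of the main effect.
- 95% CI half-width = 2.086 × 0.675 = 1.41 SD.
- A difference of about 2.0 SD is needed for 80% power.

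**Sensitivity to baseline.** The planned model has repeated measurements over time, so baseline may add precision. The protocol gives no baseline correlation, so r below is an assumed class-level value, and the SE is 0.675 × √(1 − r²). Miss rates are from the noncentral t with 20 df.

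| Class-level r | SE (SD) | Misses 0.5 SD | Misses 1.0 SD |
|---|---|---|---|
| 0 | 0.675 | 89% | 71% |
| 0.5 | 0.584 | 87% | 63% |
| 0.8 | 0.405 | 78% | 35% |

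A simulation of the unadjusted case (20,000 runs) gave 29.0% power at 1.0 SD, which agrees with the 71% miss rate.

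**Other sensitivities.**
- Unequal split, 16 classes of one gender and 8 of the other, r = 0: SE = √(.683 × (2/4 + 2/8)) = 0.716 SD, with miss rates of 90% and 73%.
- ICC of only .10 (assumed): class-mean variance = .10 + .90/7 = .229 and SE = √(4 × .229/6) = 0.390 SD. A 0.5-SD difference is missed 77% of the time at r = 0 and 47% at r = 0.8.
- Mixed-sex classes, 3.5 boys and 3.5 girls measured on average, with no class-to-class variation in the gender gap: SE = √(.37 × 2/3.5 × 2/12) = 0.188 SD. A 0.5-SD difference is then missed about 28% of the time (22 df) and a 0.8-SD difference about 2%.

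**The case against.** **The protocol does not say that p > .05 will be called homogeneity.** This is correct. A reader might infer it from the verb determine combined with a .05 criterion, but no sentence says so, the Discussion says explore, and gender homogeneity is not among the stated objectives or hypotheses. Nor does the Discussion say that a null interaction would support one programme for both sexes; that too would be the reader's inference. What stands is narrower: the stated aim cannot be met by the stated test.

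**A condensed article may leave margins, intervals and degrees of freedom to a fuller document.** This is also correct, and their absence is not the point. The point is the aim and criterion that the article does state.

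**The unadjusted figures are not the planned analysis.** This has force. Baseline is measured over three lessons, the model includes time, and pairs are matched on baseline MVPA. With a class-level correlation of 0.8, a 1.0-SD difference is usually detected. It would be too strong to say that large differences are missed most of the time whatever the baseline gain. A 0.5-SD difference, however, is still missed 78% of the time at the protocol's ICC.

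**Six per cell is inferred.** It is, and the model refers to student gender while the word unisex is ambiguous. If lessons were mixed-sex, the concern would largely disappear. Matching on class gender speaks against that reading.

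**The motivation outcomes use the same interaction term.** One might carry the criticism over to them. The documents do not support that: homogeneity is not the stated aim there, and no ICC is given for them.

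**Conclusion.** The point holds in a limited form. In this design, a non-significant group × gender test on MVPA cannot establish that the effect is the same in boys and girls, so the aim in the Statistical methods section claims more than the test can deliver and more than the Discussion claims.

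The logical part rests on no assumption. Its size rests on single-sex classes in roughly equal numbers, the protocol's ICC of .63 and the unknown gain from baseline. Over assumed correlations from 0 to 0.8, the 95% CI half-width runs from 1.41 down to 0.84 SD (2.086 × 0.405). Even at the favourable end, the interval extends to gender differences nearly as large as the whole planned effect of 1.0 SD. The main comparison keeps about 81% power, so the shortfall is specific to the interaction.

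**What to change.** In the Statistical methods section, replace the aim of determining homogeneity with an exploratory estimation aim. For MVPA, report the intervention effect in boys, the effect in girls and the difference between them, each with a 95% confidence interval whose degrees of freedom are based on classes. State that p > .05 for group × gender will not be reported as homogeneity. This brings the section into line with the Discussion.

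A formal equivalence margin is not recommended. The expected 90% CI half-width is 1.725 × 0.675 = 1.16 SD without baseline gain and 1.725 × 0.405 = 0.70 SD with a correlation of 0.8. A margin such as ±0.5 SD could hardly ever be met, even with no true difference.

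The cost is a change of wording and a few contrasts from a model already planned. No further classes, students or data are needed, and the primary analysis and sample size do not change. The downside is that the gender question will probably be reported as unresolved.
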